## Abstract

**Background:**

Perinatal asphyxia is, even in developed countries, one the major causes of neonatal morbidity and mortality. Therefore, if foetal distress during labour is suspected, one should try to restore foetal oxygen levels or aim for immediate delivery. However, studies on the effect of intrauterine resuscitation during labour are scarce. We designed a randomised controlled trial to investigate the effect of maternal hyperoxygenation on the foetal condition. In this study, maternal hyperoxygenation is induced for the treatment of foetal distress during the second stage of term labour.

**Methods/design:**

This study is a single-centre randomised controlled trial being performed in a tertiary hospital in The Netherlands. From among cases of a suboptimal or abnormal foetal heart rate pattern during the second stage of term labour, a total of 116 patients will be randomised to the control group, where normal care is provided, or to the intervention group, where before normal care 100% oxygen is supplied to the mother by a non-rebreathing mask until delivery. The primary outcome is change in foetal heart rate pattern. Secondary outcomes are Apgar score, mode of delivery, admission to the neonatal intensive care unit and maternal side effects. In addition, blood gas values and malondialdehyde are determined in umbilical cord blood.

**Discussion:**

This study will be the first randomised controlled trial to investigate the effect of maternal hyperoxygenation for foetal distress during labour. This intervention should be recommended only as a treatment for intrapartum foetal distress, when improvement of the foetal condition is likely and outweighs maternal and neonatal side effects.

**Trial registration:**

EudraCT, 2015-001654-15; registered on 3 April 2015. Dutch Trial Register, NTR5461; registered on 20 October 2015.

**Electronic supplementary material:**

The online version of this article (10.1186/s13063-018-2567-x) contains supplementary material, which is available to authorized users.

## Background

Labour contractions cause alterations in intrauterine pressure and can thereby affect uterine and umbilical blood flow [1–5]. These fluctuations in blood flow towards the foetus can negatively influence oxygen flow and blood pressure [1–5]. Through chemo- and baroreceptor responses, these changes in foetal oxygenation and blood pressure affect foetal heart rate (FHR) [1, 2, 6, 7]. Hence, non-reassuring FHR patterns such as FHR decelerations may be a sign of foetal hypoxia [8–10]. Prolonged foetal hypoxia may lead to an increased risk of foetal morbidity, including renal insufficiency, pulmonary hypertension, necrotising enterocolitis and hypoxic–ischemic encephalopathy and foetal death [11, 12]. A prospective cohort study of term neonates in 2010 showed that 48% of admissions of these neonates to neonatal intensive care units (NICUs) were related to perinatal asphyxia (defined by the authors as a 5-minute Apgar score < 7). The neonatal mortality rate was 8% in this study, the largest proportion of which (71%, *n* = 12 of 17) was related to asphyxia [13].

Methods to directly measure foetal oxygenation during labour are unavailable, whereas methods for the continuous intrapartum monitoring of pH, oxygen saturation (SpO_2_), partial carbon dioxide pressure (pCO_2_) and partial oxygen pressure (pO_2_) are not yet suitable for clinical practice [14–16]. Therefore, the cardiotocogram (CTG), with occasional foetal scalp blood sampling (FSBS), is still the method of first choice to estimate foetal well-being during labour. The CTG has very good specificity but poor sensitivity for foetal well-being [17]. In other words, if the FHR pattern is reassuring, the foetus is very likely to be well-oxygenated. However, when FHR patterns are non-reassuring, the foetal condition is unclear, and foetal distress cannot be ruled out.

Instead of aiming for immediate delivery in the presence of suspected foetal distress, one may try to improve foetal oxygenation to avoid an invasive intervention. Several intrauterine resuscitation techniques are used in clinical practice and have been described in the literature [18, 19]. However, robust evidence regarding their effect on neonatal outcome is limited [18]. One of the interventions that still raises discussion is the administration of additional oxygen to the mother to treat foetal distress during labour [18, 20–23].

### Summary of findings from clinical studies

In the past five decades, researchers in several studies have investigated the effect of maternal hyperoxygenation on maternal and foetal oxygenation. Indeed, they found increasing maternal pO_2_ [24] and foetal SpO_2_ and pO_2_ levels, but unfortunately these studies were mainly performed in the non-compromised foetus [25–27]. Furthermore, only a few non-randomised studies of poor quality have been performed in the distressed foetus [28–32]. These studies suggest an improvement in FHR patterns and foetal scalp pH when 100% oxygen is applied to the mother. Based on these publications, authors of a Cochrane review published in 2012 concluded that ‘there is not enough evidence to support the use of prophylactic oxygen therapy for women in labour, nor to evaluate its effectiveness for fetal distress’, owing to the lack of randomised controlled trials (RCTs) [33].

An important concern in the use of maternal hyperoxygenation for foetal distress is the potential negative effect on umbilical cord pH. In a study by Thorp et al. [34], 86 term parturients were randomised to receive additional oxygen or normal care during the second stage of labour. The main outcome measures were cord blood gas and co-oximetry values. The mean cord blood gas values did not significantly differ between the intervention and control groups. However, Thorp et al. found significantly more arterial pH values < 7.20 in the group receiving extra oxygen. The lowest pH in arterial blood gas (pHa) value that they found was 7.09. They also found that the duration of oxygen therapy was inversely related to arterial cord pH, whereas Apgar scores and hospital admission rates did not differ between the groups. They concluded that prolonged oxygen treatment during the second stage of labour leads to a deterioration of cord blood gas values at birth. An important fact is that only patients with reassuring FHR patterns were included in their study. Therefore, (ominous) foetal hypoxia at the start of oxygen delivery was very unlikely. Thus, their study did not address the effect of maternal hyperoxygenation in cases of suspected foetal distress.

Another frequently stated argument to discourage maternal hyperoxygenation as standard care is the potential increase in free oxygen radicals in both mother and foetus [35, 36]. An increase in the markers for free oxygen radical production has been seen for the use of high fractions of inspired oxygen and in the presence of non-reassuring FHR patterns [35–38]. Also, lipid peroxide concentrations in arterial cord blood are higher after uncomplicated vaginal delivery than after elective caesarean section [39].

To a certain degree, free oxygen radicals are physiological and known to be higher in the presence of several maternal and foetal conditions, such as pre-eclampsia, diabetes, smoking, intrauterine growth restriction and foetal distress [37, 39–42]. The effect of maternal hyperoxygenation on free oxygen radical release, in response to non-reassuring foetal status, has not yet been investigated.

What we do know is that neonatal resuscitation with 100% oxygen may lead to an increase in neonatal mortality and morbidity, including bronchopulmonary disease and retinopathy, mainly in premature infants [43–46]. However, the increase in foetal pO_2_ due to maternal hyperoxygenation will never reach the levels obtained by the direct application of 100% oxygen directly to the foetus [23]. To our knowledge, the clinical implication of increased free radical production due to maternal hyperoxygenation has not been investigated. Researchers in studies using maternal hyperoxygenation as a treatment for the growth restricted foetus did not report any harmful effects [47, 48].

With regard to the mother, some potential side effects have to be taken into account. The use of high fractions of inspired oxygen in the absence of tissue hypoxia may cause toxic effects as a result of oxidative stress [49, 50]. This may lead to, for example, mucosal inflammation, hypoperfusion and pneumonitis [51]. A reversible vasoconstriction of approximately 10% in the maternal brain has been described [52]. However, this is not expected to cause any harm [53, 54]. Administration of 100% oxygen during labour is not investigated. However, it has been well investigated for the treatment of cluster headaches, and no severe side effects (e.g., hypoventilation and fainting) have been reported [54].

Inhaling high fractions of inspired oxygen will increase the concentration of free oxygen radicals in maternal blood [35]. Despite the adverse effects of free oxygen radicals that have been described [55], it is unlikely these will cause clinically relevant tissue damage, owing to the mature anti-oxidant system in the adult [35, 36]. Also, the Dutch Pharmacovigilance Centre Lareb has not been informed of any side effects of oxygen therapy [56].

### Current recommendations on the use of maternal hyperoxygenation

On the basis of current knowledge, it is difficult to determine whether the beneficial effects of maternal hyperoxygenation outweigh the potential side effects. As a consequence, recommendations in international guidelines and use in clinical practice are non-uniform [20]. Maternal hyperoxygenation during labour is often used in the United States to increase oxygen transport towards the foetus [21]. The American College of Obstetricians and Gynecologists guideline on foetal resuscitation recommends the administration of oxygen to the mother in cases of foetal distress [57]. In contrast, the Royal College of Obstetricians and Gynaecologists explicitly states in their Green Top Guideline not to apply maternal oxygenation for reasons other than maternal hypoxia, until the beneficial effect is proven [58]. A recent discussion on benefit and harm of maternal hyperoxygenation in the *American Journal of Obstetrics and Gynecology* emphasised the current lack of evidence [21–23]. In fact, several reviews underline an urgent need for an RCT investigating the effect of maternal hyperoxygenation on the foetal condition [21–23, 33].

## Methods/design

### Aim

The aim of this study is to investigate the effect of maternal hyperoxygenation with 100% oxygen on the foetal condition during the second stage of labour in the presence of suspected foetal distress during term labour. Also, we will investigate the potential side effects to formulate recommendations for international clinical practice and future research.

### Study design

This study will be a single-centre RCT performed in a tertiary hospital in The Netherlands. We are comparing maternal hyperoxygenation for the treatment of foetal distress during the second stage of labour with conventional care. All procedures and time frames are displayed in Fig. 1 according to the Standard Protocol Items: Recommendations for Interventional Trials (SPIRIT) [59]. Additional file 1 contains the complete SPIRIT checklist.

**Fig. 1 Fig1:**
[figure not shown]
The schedule of forms and procedures, according to the Standard Protocol Items: Recommendations for Interventional Trials (SPIRIT). *CRF* Case report form, *CTG* Cardiotocogram, *FHR* Foetal heart rate, *MDA* Malondialdehyde, *SAE* Serious adverse event, SUSAR Suspected unexpected serious adverse reaction

### Participants

The study population will be drawn from among parturients admitted to the labour ward of a tertiary hospital (Máxima Medical Centre, Veldhoven, The Netherlands), where approximately 2200 deliveries occur annually, of which approximately 1900 are term births. CTG and, if necessary, FSBS are generally used for foetal monitoring during labour. Maternal repositioning, discontinuation of administration of oxytocin, use of tocolytic drugs and intermittent pushing are common interventions used to achieve intrauterine resuscitation, whereas amnioinfusion and maternal hyperoxygenation are never applied as standard care in our centre.

### Inclusion criteria

Pregnant women ≥ 18 years old in term labour and with an intended vaginal delivery of a singleton in cephalic presentation can participate in this study.

### Exclusion criteria

Exclusion criteria are determined with a focus on the risk of excessive production of free oxygen radicals and reducing the influence of other factors affecting FHR pattern. These are recent use of any of the following medications: corticosteroids, anti-hypertensives, magnesium sulphate, amiodarone, opioids, adriamycin, bleomycin, actinomycin, menadione, promazine, thioridazine or chloroquine. Other exclusion criteria are the use of tobacco, recreational drugs or alcohol during pregnancy. Parturients with pre-existing cardiac disease, pulmonary disease with the use of medication, diabetes, hyperthyroidism or anaemia (haemoglobin < 6.5 mmol/L or 10.5 g/dl) will also be excluded. Foetal factors leading to exclusion are suspected infection during labour (need for antibiotics), congenital malformations and normal or pre-terminal FHR pattern, or prolonged bradycardia (according to the modified International Federation of Gynecology and Obstetrics [FIGO] classification; *see* Table 1) [60, 61].

**Table 1 Tab1:** Classification of cardiotocograms according to the modified International Federation of Gynecology and Obstetrics criteria

	Baseline heart frequency	Variability Reactivity	Decelerations
Normal CTG	• 110–150 bpm	• Accelerations • 5–25 bpm	• Early uniform decelerations • Uncomplicated variable decelerations (loss of < 60 beats)
Intermediary CTG	• 100–110 bpm • 150–170 bpm • Short bradycardia episode < 100 bpm for > 3 minutes < 80 bpm for > 2 minutes	• > 25 bpm (saltatory pattern) • < 5 bpm > 40 minutes	• Uncomplicated variable decelerations (loss of > 60 beats)
	• A combination of two or several intermediary observations will result in an abnormal CTG		
Abnormal CTG	• > 170 bpm • Persistent bradycardia < 100 bpm for > 10 minutes < 80 bpm for > 3 minutes (without an increasing tendency)	• < 5 bpm for > 60 minutes • Sinusoidal pattern	• Complicated variable decelerations with a duration of > 60 seconds • Repeated late uniform decelerations
Pre-terminal CTG	• Total lack of variability (< 2 bpm) and reactivity with or without decelerations or bradycardia		

*bpm* Beats per minute, *CTG* Cardiotocogram

### Patient recruitment and randomisation

All patients eligible to be included in this study will be asked antepartum to participate when they visit the outpatient clinic or when they are admitted to the delivery ward. All patients will receive oral and written information about the study from the attending midwife or doctor or from a co-investigator (Additional files 2 and 3). After informed consent is obtained, and only in case of suboptimal or abnormal FHR patterns during the second stage of labour, randomisation is performed using sealed opaque envelops. The allocation sequence is computer-generated using random blocks of four or six patients.

### Intervention and control groups

Patients will randomly be assigned to one of the two arms of the study:*Control group*: Normal care (according to local standards) is provided, and preferably started at least 10 minutes after the onset of a suboptimal or abnormal FHR pattern, according to the modified FIGO criteria (Table 1) [60, 61].*Intervention group*: In case of a suboptimal or abnormal FHR pattern according to the modified FIGO criteria, 100% oxygen is applied to the mother at 10 L/minute via a non-rebreathing mask and continued until delivery. Co-interventions (normal care) may be initiated after 10 minutes of oxygen administration without a satisfactory effect on FHR to investigate the effect of only maternal hyperoxygenation on FHR, without risking prolonged foetal hypoxia. In case a patient needs to undergo a caesarean section, oxygen administration will be continued until the baby is born.

Obviously, in any case where the delivery room staff believe additional interventions should be applied for safety reasons, the study protocol can be overruled at any time.

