#### What is the time frame of interest?

All patients serve as their own control, with changes in FHR being compared before and after the start of the study protocol, regardless of whether the patients belong to the control or the intervention group. Results in the intervention group and the control group will also be compared.

For the analysis where patients serve as their own control, the time frames of interest for outcomes related to changes in FHR are as follows:*Control group*: 10 minutes before and after the start of the study protocol. In total, 20 minutes of data will be analysed (Fig. 2).*Intervention group*: 10 minutes before the start of the study protocol up to 15 minutes after the start of the study protocol. The time frame of interest after the start of the study protocol is determined as the period between 5 and 15 minutes after maternal hyperoxygenation is initiated, motivated by the expectation that it will take 5 minutes for maternal pO_2_ to increase to a maximum of approximately 475 mmHg [24]. After that, the effect of the intervention will be observed for 10 minutes. In total, 20 minutes of data will be analysed (Fig. 3).

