**Fig. 3 Fig3:**
[figure not shown]
The time frame of interest for analysis of outcome measures where patients serve as their own control: the intervention group

These periods are established because during this period, maternal hyperoxygenation can be compared with no treatment. Furthermore, we will also compare the periods from the start of the study until birth, although these results may be influenced by other interventions that may have been applied.

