## Discussion

This study is the first RCT to investigate the effect of maternal hyperoxygenation for foetal distress during labour [18, 33]. So far, the effects of supplemental oxygenation in the presence of FHR abnormalities have been investigated only in small, non-randomised studies. Because of the lack of concrete results from clinical trials, it is hard to compare the beneficial effects of maternal hyperoxygenation with the potential side effects. As a result, recommendations on the use of this intervention for foetal distress in international guidelines are non-uniform [20]. Thus, the results of this study will help to filling an internationally recognised ‘research gap’.

We believe patient safety is carefully addressed in this study, and ethical concerns are limited. One of the major concerns of administering high fractions of oxygen is the increase in free oxygen radicals. Whether this has a clinical effect remains unclear. We excluded from this study all patients with a higher a priori risk of exposure to increased free oxygen radical levels.

Both practical and safety issues led to limitations of this study. An important limitation is the primary outcome measure. We recognise that changes in FHR as a primary outcome measure are not optimal, because FHR does not accurately reflect foetal oxygenation and acid-base balance [60, 74, 75]. However, we believe this is the best available method to record changes in the foetal condition during labour. Furthermore, we assume that if no beneficial effect on FHR can be shown, an improvement in neonatal outcome is unlikely. Ideally, neonatal outcome measures such as Apgar score and umbilical cord pH are the outcome measures of first choice. However, a study with appropriate power to address these outcome measures would need a very large sample size. Because the potentially harmful effects have not been investigated properly yet, we chose not to expose a large group of women and their foetuses to this intervention. If a positive effect on FHR pattern without severe side effects can be confirmed by this study, we will perform a larger multicentre RCT to investigate the effect on Apgar score and cord blood gas values.

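### Normal care is permitted from minute 10 of oxygen, but the oxygen arm is analysed over minutes 5-15, so the claimed comparison with no treatment is not secured

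*Protocol article*

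**What the plan says.** All of this is in the protocol article.

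- **Oxygen arm, care rule** (Intervention and control groups): "Co-interventions (normal care) may be initiated after 10 minutes of oxygen administration without a satisfactory effect on FHR". The stated purpose is to isolate the effect of oxygen without prolonging foetal hypoxia.
- **Oxygen arm, analysis window** (What is the time frame of interest?): "the period between 5 and 15 minutes after maternal hyperoxygenation is initiated", compared with the 10 minutes before the start. The 5-minute lag allows maternal pO2 to reach its expected maximum.
- **Control arm**: the window is 10 minutes before and 10 minutes after the start of the study protocol. Normal care is "preferably started at least 10 minutes after the onset of a suboptimal or abnormal FHR pattern".
- **Either arm**: if staff see a safety reason, "the study protocol can be overruled at any time".
- **Scope of the windows**: they are introduced with "For the analysis where patients serve as their own control". The same section adds that the two arms will also be compared.
- **Rationale** (the text after Fig. 3): the periods were chosen "because during this period, maternal hyperoxygenation can be compared with no treatment". The start-to-birth comparison is then reported with the caution "although these results may be influenced by other interventions that may have been applied". The windowed comparison carries no such caution.

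**The concern.** The hold on normal care in the oxygen arm ends at minute 10, while the window said to show oxygen against no treatment ends at minute 15. The care allowed in between goes only to women whose trace has not responded. It consists of measures that the Participants section lists as usual intrauterine resuscitation: repositioning, stopping oxytocin, tocolysis and intermittent pushing. If that care works, the oxygen arm's before-after change includes it.

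The interpretation matters because the Discussion attaches a decision to each result. On the positive side: "If a positive effect on FHR pattern without severe side effects can be confirmed by this study, we will perform a larger multicentre RCT". On the negative side, it would advise against using oxygen for foetal distress.

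**Working it through.** **1. The plan's own figure.** Oxygen arm, minutes analysed: 10 before the start + (15 − 5) after = 20. This reproduces the stated 20 minutes, 10 of them after the start.

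**2. Overlap with permitted care.** Both times count from the start of oxygen. Care may begin at minute 10 and the window runs to minute 15: (15 − 10)/(15 − 5) = 5/10 = 50%. This is the ceiling under the scheduled rule. Responders contribute nothing to it, and care that starts or acts later contributes less. The safety override could bring care in before minute 10.

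**3. Control window.** If care waits 10 minutes from the start of the study protocol, the overlap with minutes 0-10 is 0. That is not guaranteed: the delay is only a preference, and it runs from onset of the FHR pattern, not from protocol start.

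**4. Is this handled elsewhere in the article?** No section delays care to minute 15, stops the trace at a co-intervention, or treats co-interventions in the analysis. The per-protocol set (Data analysis) depends on receipt of oxygen and wrongful inclusions only.

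**5. Illustration of size. Every input here is assumed.** Let a share *q* of the oxygen arm receive care that improves the outcome by *e* points from minute *t*.

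Gain in the oxygen arm's own-control improvement = *q* × *e* × (15 − *t*)/10.

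| *q* | *e* | *t* = 10 | *t* = 12 |
|---|---|---|---|
| 0.5 | 40 | 10 | 6 |
| 0.5 | 20 | 5 | 3 |
| 0 | any | 0 | 0 |

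If the same windows were used between arms, care in a share *qc* of controls from minute *tc* would add *qc* × *e* × (10 − *tc*)/10 to the control arm. With *e* = 40 and *tc* = 0, the net (oxygen minus control) is:

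| *q* | *qc* | control gain | net, *t* = 10 | net, *t* = 12 |
|---|---|---|---|---|
| 0.5 | 0 | 0 | +10 | +6 |
| 0.5 | 0.25 | 10 | 0 | −4 |
| 0.5 | 0.5 | 20 | −10 | −14 |
| 0 | 0.5 | 20 | −20 | −20 |

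The sign depends on inputs that the article does not give.

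**6. What a minutes 5-10 window would do.** It ends before scheduled rescue, so the oxygen-arm term is 0 unless the override is used. Early control care still enters: net = −*qc* × *e* × (10 − max(*tc*, 5))/5. With *e* = 40 and *tc* ≤ 5 this is −10 for *qc* = 0.25, −20 for *qc* = 0.5, and 0 with no control care.

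**7. Precision of that window.** The SD of 50 points and the 50-point effect come from Sample size calculation. There, 67 patients per FHR stratum means 33.5 per arm. Two assumed noise models for a 10-minute baseline and a 5-minute follow-up:

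- independent noise per minute: √[(1/10 + 1/5)/(1/10 + 1/10)] = 1.22, SD 61;
- 3 decelerations in 10 minutes and 1 in 5: √[(1/3 + 1)/(2/3)] = 1.41, SD 71.

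Neither is an upper bound. Two-sided 0.05 noncentral-t power at 33.5 per arm:

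| Effect in the window | SD 50 | SD 61 | SD 71 |
|---|---|---|---|
| 50 points | 98% | 91% | 81% |
| 37.5 points (assumed dilution) | – | about 70% | about 57% |

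At 67 per arm and 50 points, power is at least 98% under either model. A Mann-Whitney test, with the 3/π efficiency adjustment, would lower these figures slightly (81% becomes about 80%).

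**The case against.** The strongest reply is that the 50% measures permission, not exposure. Care may start only in non-responders, and it must then be decided on, given and take effect. This stands: the share of outcome minutes actually changed is unknown and may be small.

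Second, the windows are assigned to the own-control analysis, whereas the primary outcome compares arms. This also stands. A reader might infer that the randomised primary comparison is biased in favour of oxygen. The documents do not support that. Use of these minutes for the primary outcome is a plausible reading, since the arms are also to be compared and the periods are justified as oxygen against no treatment, but it is not stated. Even on that reading, early care in controls could reverse the sign.

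Third, the care rule is a deliberate safety compromise, and the override and the soft control-arm delay are unavoidable in suspected foetal distress. Agreed, and nothing here asks for them to change.

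Fourth, co-intervention logging and sensitivity analyses may be in the full protocol or the analysis plan, which are not shown. Their absence from the article is not the point. What does not stand is the rationale itself: the article fixes both times and states a property that they do not deliver. A further analysis elsewhere would not make that sentence correct.

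Finally, a 5-10 minute window keeps only the first half of the period chosen for observing the effect, and could dilute a slow foetal response. This is right, and it is why that analysis should not act as a gatekeeper.

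**Conclusion.** The concern holds as a conflict between a stated rationale and the plan's own care rule. Up to 5 of the oxygen arm's 10 outcome minutes are open to scheduled, response-triggered normal care, so the 5-15 minute window does not secure a comparison of oxygen alone with no treatment. This rests on the article's clock times and needs no assumption.

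The consequence is direct for the oxygen arm's own-control comparison, where effective rescue care would inflate the apparent improvement. Its size cannot be derived from the documents; the 3 to 10 points above are conditional on assumed inputs, and with no rescue the gain is 0. For the between-arm comparison the documents establish neither that these windows are used nor the direction of any net effect. This should be fixed because the remedy is cheap and the interpretation feeds the Discussion's stated decisions. It is not evidence of a demonstrated bias.

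**What to change.** Leave the care rule and the 5-15 minute window as they are.

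1. Reword the rationale after Fig. 3: minutes 10-15 of the oxygen arm, and any early normal care in controls, may include co-interventions. Interpret the 5-15 minute result as oxygen plus normal care where needed.
2. Report the number and timing of co-interventions by arm.
3. Add a supporting analysis of minutes 5-10, the same minutes in both arms, with deceleration burden expressed per minute of trace. Read it together with the co-intervention times in both arms. It should not decide whether an effect is attributed to oxygen, and a null result in it must not by itself rule one out, because of noise, possible dilution and possible early care in controls.
4. If traces are also censored at the first co-intervention, keep that as a sensitivity analysis only, since the censoring depends on response.

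The cost is a wording change, a record of co-intervention times and a second extraction from the digital traces. The statistical cost is the loss of precision shown under working: within one FHR stratum, about 91% or 81% power for a 50-point effect, and about 70% or 57% if the effect in those minutes is 37.5 points.
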